### 3.5. Statistical methods

#### 3.5.1. Power analysis.

We computed power to detect differences in a larger reduction of PFC activity during personalized, compared to fixed, tactile cueing. Furthermore, we predict that personalized cueing will show less activation of PFC versus fixed cueing (i.e., more automatic). We conservatively assume 54 subjects, 27 for each group (personalized and fixed training), will be included in this analysis, based on recruitment of 60, and allowing for modest dropout (> 10%). We computed power for a repeated-measures ANOVA model with 1 between and 1 within subject effect based on the Geisser-Greenhouse F-test (equivalent to a mixed model). Using patterns of HbO2 levels comparable to previously published results(ref Stuart and Mancini JNPT), assuming between-subject variance of 0.08, modest intra-subject correlation of 0.2, and level of significance at 0.05, we find that power is 82% for the test of between-subject effects (cueing group comparison), and 94% for the test of interaction (differential impact of dual-task versus single-task walking between the personalized- and fixed-cueing groups).

We also computed sample sizes required to achieve at least 80% power for detecting group differences of at least 0.50 SD for measures of walking and turning in daily life with ANCOVA models, conservatively assuming covariate R2 equal to 20%. We set level of significance to 0.02, which is the average alpha level when employing the Holm correction method over 6 outcomes (see below). Under these assumptions, 36 patients (18 per arm) are required to achieve 81.2% power. Thus, our plan to recruit 30 per arm will result in adequately-powered tests while allowing for missing/insufficient data or patient dropout. One of the goals of this trial is to generate preliminary estimates of sensitivity of daily life gait and turning quality due to a cueing intervention. These estimates ultimately will be used to inform power and sample size computations for a larger clinical trial. The small intervention proposed here (30 per group) is not designed to be a highly powered trial itself, but will make use of a randomized, two-group intervention design. All computations were conducted using PASS v15 (PASS 15 Power Analysis and Sample Size Software (2017), NCSS, LLC).

We are not planning interim analysis, and we are not expecting to stop the recruitment early.

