#### 3.5.2. Statistical analysis.

The primary outcome will compare PFC and sensory cortex HbO2 while walking and turning between personalized tactile cueing and fixed tactile cueing groups measured during Laboratory Visit 1, without and with cueing. We will average the HbO2 concentrations over 2-minutes of walking (and over 1-minute of 360-degree clockwise and counterclockwise turning), then compare within-subject effects (baseline versus cueing) and between-subject effects (personalized versus fixed cueing) in a repeated measures analysis. Specifically, we will apply mixed-effects models with HbO2 levels (averaged over walking bout) for each person at each assessment time point as the dependent variable. We will include as independent variables: (i) indicator variable for group assignment (personalized or fixed cueing), (ii) indicators for time points (baseline, cueing), and (iii) group by assessment interaction terms. Randomization stratification variables, Hoehn and Yahr, FOG and cognitive status, will be entered into the model as covariates. A random subject intercept will account for correlation between the two repeated measurements within each subject.

Similar linear mixed effects models will be used to demonstrate improvement in walking and turning metrics in the laboratory (carried out with the fNIRS measurements), secondary outcomes. Significance level will be set at 0.05 for testing whether coefficients are different from 0 for primary and secondary outcomes.

We will employ similar linear mixed effects models to investigate whether the two cueing modalities will result in different improvements of walking and turning during daily life. This is an exploratory analysis. For the week of daily mobility without and with cueing, we will summarize walking and turning measures at home (outlined on Table 1) by computing the average over 7 days of daily activity, considering only the recordings with more than 7 hours per day and at least 5 days (Table 1). Randomization stratification variables, Hoehn and Yahr, freezing of gait and cognitive status, will be entered into the model as covariates. Additional covariates would be the life space assessment and activity levels. The effect sizes from models fit for this pilot study will be used to determine the number of subjects required for a future clinical trial.

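### The stated 81.2% power for a 0.50 SD daily-life group difference is wrong: 18 per arm gives about 24%, and with the other stated inputs 81% needs a difference of 1.0 SD.

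*Protocol article*

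**What the plan says.** Section 3.5.1 (Power analysis) gives a second calculation, apart from the one for prefrontal activity. Its target is a power of 80% or more, and the task is described as "detecting group differences of at least 0.50 SD for measures of walking and turning in daily life with ANCOVA models". The covariates are taken to explain a fifth of the variance (R² of 0.20). On the type I error it says: "We set level of significance to 0.02, which is the average alpha level when employing the Holm correction method over 6 outcomes". The result is "Under these assumptions, 36 patients (18 per arm) are required to achieve 81.2% power", and the conclusion drawn from it is "Thus, our plan to recruit 30 per arm will result in adequately-powered tests while allowing for missing/insufficient data or patient dropout".

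The same paragraph says that the trial is not meant to be highly powered and that it should yield preliminary estimates. Section 3.5.2 calls the daily-life analysis exploratory and adds: "The effect sizes from models fit for this pilot study will be used to determine the number of subjects required for a future clinical trial".

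**The concern.** A half-SD difference between two independent groups ordinarily needs more than 60 per arm for 80% power at the 5% level. A covariate that explains 20% of the variance lowers this by about a fifth, and a significance level of 0.02 raises it again. A requirement of 18 per arm is therefore implausible on sight.

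Three things depend on the figure:

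- Readers are told that the home comparison can detect 0.50 SD. A non-significant home result could then be taken as evidence against an effect of that size.
- A requirement of 18 per arm makes losses look harmless. The outcome-measures section excludes participants from the home analysis for too little sensor wear or too little cueing use, so the evaluable number may fall well below 30 per arm.
- The home estimates are to inform the size of a later trial. If the same misreading of the effect size were carried forward, that trial would be too small by a factor of more than three (66 against 18 per arm).

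**Working it through.** **Inputs (all from section 3.5.1 unless noted).** Group difference d = 0.50 SD; covariate R² = 0.20; α = 0.02; n = 18 per arm; 1:1 allocation (section 3.1). Sidedness is not stated. The ANCOVA F-test is two-sided, so two-sided is the main reading and one-sided is tried as a variant. The number of covariates is not stated; one is used here, and 0 to 5 were tried.

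**Check of α.** The average Holm level over six outcomes is 0.05 × (1 + 1/2 + 1/3 + 1/4 + 1/5 + 1/6)/6 = 0.0204. The stated 0.02 agrees with its stated origin.

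**Formula.** In SD units, the standard error of the adjusted difference is √[(1 − R²) × 2/n]. The noncentrality is d divided by that standard error. Power comes from the noncentral t distribution with 2n − 3 degrees of freedom (one covariate).

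**Stated inputs, 18 per arm.**
- Standard error = √(0.8 × 2/18) = 0.298
- Noncentrality = 0.50/0.298 = 1.677
- Degrees of freedom = 33; two-sided critical value at 0.02 = 2.445
- Power = **23.7%** (23.4% to 23.7% across 0 to 5 covariates), against the stated 81.2%

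**Attempt to recover 81.2%.** With d = 1.0 and all else unchanged, the noncentrality is 1.0/0.298 = 3.354. Power is then 81.3% with one covariate and 81.2% with two, and 18 is the smallest n per arm that reaches 80%. For two equal groups, the SD of the group means is half their difference, so f = 0.50 corresponds to d = 1.0. An R² of 0.80 with d = 0.50 gives the same result, because 0.50²/0.20 = 1.0²/0.80 = 1.25.

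**Favourable readings at d = 0.50.**

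| Variant | Power |
|---|---|
| One-sided α 0.02, 18 per arm | 33.4% |
| Two-sided α 0.05, 18 per arm | 37.0% |
| One-sided α 0.05, 18 per arm | 49.9% |
| 36 per arm instead of 36 in total, two-sided α 0.02 | 50.0% |

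None comes near 81.2%.

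**What the design delivers** (R² 0.20, two-sided).

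| n per arm | Power at 0.50 SD, α 0.02 | Power at 0.50 SD, α 0.05/6 = 0.0083 | Difference with 80% power, α 0.02 |
|---|---|---|---|
| 18 | 23.7% | 14.7% | 0.99 SD |
| 27 | 37.2% | 25.7% | 0.79 SD |
| 30 | 41.6% | 29.5% | 0.75 SD |

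The 0.0083 column is the level that the smallest of six p-values must meet under Holm. It is shown for scale and is not needed to establish the error.

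**Sample size for 0.50 SD at α 0.02.** 65 per arm gives 79.6% and 66 per arm gives 80.3%, so 66 per arm (132 in total) is required, against the stated 36 in total.

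**Precision.** At 27 per arm the standard error is √(0.8 × 2/27) = 0.243. The 95% confidence interval half-width (t, 51 degrees of freedom) is about 0.49 SD, as wide as the effect the plan names.

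**The case against.** The best defence is that little hangs on the number. The daily-life outcomes are labelled exploratory throughout, and the power section itself disclaims high power. The planned 60 participants also rest on the separate prefrontal calculation, which assumes 54 analysed. The Discussion already expects that a small effect would call for a larger later trial. Correcting the figure changes no primary test, decision rule or enrolment target. All of that stands, and it limits the consequence. It does not make the figure right, and the same paragraph still tells the reader that the tests are adequately powered.

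A second objection concerns cause. The Cohen's f explanation is not proven, since an R² of 0.80 yields the same power. If 0.50 was meant as f, the calculation is sound and the description of the effect is wrong. This also stands. The sponsor should check the software inputs. On either account, the assumptions as printed do not give 81.2%.

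Third, 27 per arm is the protocol's assumption for the laboratory analysis. The home analysis has its own exclusions and could have fewer. This is a fair point: any restated power must be conditional on the evaluable number.

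Finally, the statement that effect sizes will inform a future trial does not commit the authors to using bare point estimates. That is correct, so the advice on this below is a recommendation that follows from the low precision and does not correct a second error.

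**Conclusion.** The concern holds. As printed, the inputs and the output of the daily-life power calculation disagree: power at 0.50 SD with 18 per arm is 23.7%, not 81.2%. With R² of 0.20 and α of 0.02 held, 81% needs a difference of 1.0 SD. The planned 30 per arm gives 41.6% at 0.50 SD, so a true effect of that size would be missed more often than found, and the claim of adequate power is wrong.

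This rests on a two-sided test of a two-group comparison with equal arms, the stated R² and one covariate; the number of covariates and the choice of sidedness do not alter the conclusion. It should be corrected before the figure is relied on. The effect is confined to the exploratory home comparison; the primary fNIRS power figures were not examined here.

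**What to change.** Check the inputs of the original software run, then correct section 3.5.1 in one of two ways:

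- State the effect the design can detect: with 27 to 30 evaluable participants per arm, 80% power at two-sided α 0.02 for differences of about 0.79 to 0.75 SD. The 18-per-arm figure, if kept, should be tied to a difference of about 1.0 SD.
- Or keep 0.50 SD and report power of 37% to 42% with 27 to 30 evaluable per arm.

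In either case, say that the figures depend on how many participants remain after the home-use exclusions. Delete the claim of adequate power and describe the home comparison as estimation with confidence intervals. In section 3.5.2, say that the later trial will be sized from the confidence interval, or from the observed SD and a target difference, and not from the point estimate alone.

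The cost is protocol wording, plus matching text in any statistical analysis plan that repeats the figure. No extra enrolment and no change to the primary analysis is needed. The stated power becomes less favourable.

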#### 3.5.2. Statistical analysis.

The primary outcome will compare PFC and sensory cortex HbO2 while walking and turning between personalized tactile cueing and fixed tactile cueing groups measured during Laboratory Visit 1, without and with cueing. We will average the HbO2 concentrations over 2-minutes of walking (and over 1-minute of 360-degree clockwise and counterclockwise turning), then compare within-subject effects (baseline versus cueing) and between-subject effects (personalized versus fixed cueing) in a repeated measures analysis. Specifically, we will apply mixed-effects models with HbO2 levels (averaged over walking bout) for each person at each assessment time point as the dependent variable. We will include as independent variables: (i) indicator variable for group assignment (personalized or fixed cueing), (ii) indicators for time points (baseline, cueing), and (iii) group by assessment interaction terms. Randomization stratification variables, Hoehn and Yahr, FOG and cognitive status, will be entered into the model as covariates. A random subject intercept will account for correlation between the two repeated measurements within each subject.

Similar linear mixed effects models will be used to demonstrate improvement in walking and turning metrics in the laboratory (carried out with the fNIRS measurements), secondary outcomes. Significance level will be set at 0.05 for testing whether coefficients are different from 0 for primary and secondary outcomes.

We will employ similar linear mixed effects models to investigate whether the two cueing modalities will result in different improvements of walking and turning during daily life. This is an exploratory analysis. For the week of daily mobility without and with cueing, we will summarize walking and turning measures at home (outlined on Table 1) by computing the average over 7 days of daily activity, considering only the recordings with more than 7 hours per day and at least 5 days (Table 1). Randomization stratification variables, Hoehn and Yahr, freezing of gait and cognitive status, will be entered into the model as covariates. Additional covariates would be the life space assessment and activity levels. The effect sizes from models fit for this pilot study will be used to determine the number of subjects required for a future clinical trial.

No Data Monitoring Committee was established for this study, as it was deemed low risk and of limited duration. Safety monitoring will be conducted by the principal investigator and the study team in accordance with the approved protocol

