## 2. Objectives

The primary objective of this trial is to assess immediate changes in cortical activity during walking with two types of tactile cueing in people with PD, and whether these changes are accompanied by improvement in gait and turning (laboratory testing). We hypothesize that personalized tactile cueing will reduce PFC activity (improve automaticity) and reduce gait variability (as well as improve gait and turning speed). We also expect to observe increased activity in the primary sensory cortex with this type of personalized cueing that may require sensorimotor planning. In contrast, we predict that the fixed cueing will increase PFC activity and increase gait variability (need for more attention to the cues). An exploratory objective is to evaluate the feasibility and potential benefits of using tactile cueing during daily life.

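### The personalized-versus-fixed comparison is labelled a between-subject effect in a model whose outcome includes the uncued baseline; the contrast that answers the question is in the model but is neither designated nor powered

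*Protocol article*

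**What the plan says.** Section 3.5.2 (Statistical analysis) sets out the primary comparison of prefrontal and sensory cortex HbO2 thus: the averaged values are taken and the analysts "then compare within-subject effects (baseline versus cueing) and between-subject effects (personalized versus fixed cueing) in a repeated measures analysis". The fixed effects are "i) indicator variable for group assignment (personalized or fixed cueing"), "ii) indicators for time points (baseline, cueing") and "iii) group by assessment interaction terms". The section adds: "A random subject intercept will account for correlation between the two repeated measurements within each subject". So the uncued measurement is an outcome row, not a covariate. The decision rule is: "Significance level will be set at 0.05 for testing whether coefficients are different from 0 for primary and secondary outcomes". No particular coefficient is named, and similar models are planned for the secondary laboratory outcomes and the exploratory daily-life outcomes.

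Section 3.5.1 (Power analysis) uses the same label: "power is 82% for the test of between-subject effects (cueing group comparison"). The only interaction it powers, at 94%, is group by task (dual versus single), not group by time. Yet the same section opens by giving the target as a greater reduction in prefrontal activity under personalized than under fixed cueing. Section 2 (Objectives) reads: "We hypothesize that personalized tactile cueing will reduce PFC activity (improve automaticity) and reduce gait variability", with the opposite direction predicted for fixed cueing.

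Sections 3.1 and 3.4.1 fix the order of events. Tasks are done first without cueing; the unblinded staff then configure the assigned mode; the tasks are then repeated with cueing.

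**The concern.** The question is whether the two modes change cortical activity differently from the uncued state, which is a difference in change. The effect that section 3.5.2 labels personalized versus fixed is the group effect in a model where one of the two rows per participant precedes any cue. The arms can differ on that row only by chance. Depending on coding, the labelled effect mixes a null row with the informative one, or rests on the null row alone.

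Two misreadings could follow. A chance baseline imbalance could be reported, under the plan's own label, as a difference between cueing modes. Or a real difference could be reported as no between-group effect because the labelled test sees only half of it. As several coefficients are tested against 0 and none is designated, the choice could also be made after the results are known.

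**Working it through.** **Inputs.** n = 27 per arm, within-subject correlation ρ = 0.2, significance level 0.05 (section 3.5.1). Two-sided testing and equal variances are assumed. No numeric effect size is given, so d, the arm difference under cueing in SDs of a single measurement, is an assumption.

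**What each term estimates.** Let the baseline mean be m in both arms, and the cued means m + c (fixed) and m + c + d (personalized).
- Group coefficient, baseline as reference: m − m = 0.
- Group effect averaged over both rows: (0 + d)/2 = d/2.
- Group-by-time: d − 0 = d.
- Cued difference adjusted for baseline: d.

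**The plan's own figure.** The 82% cannot be reproduced because the HbO2 means behind it are not stated. It can only be inverted. For the mean of two measurements that both carry the full difference, the variance is 0.08 × (1 + 0.2)/2 = 0.048. With 52 degrees of freedom, 82% power needs a difference of 0.175, and 0.175/√0.08 = 0.62 SD. If 0.08 is instead the between-subject component, the total variance is 0.08/0.2 = 0.40 and the difference is 0.391, again 0.62 SD. This serves only to choose an effect size for illustration.

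**Standard errors**, from √(2v/27) with unit SD:
- Averaged group effect: v = (1 + ρ)/2 = 0.60, SE = 0.211.
- Group-by-time: v = 2(1 − ρ) = 1.60, SE = 0.344.
- Baseline-adjusted: v = 1 − ρ² = 0.96, SE = 0.267.

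**Power**, noncentral t with 52 degrees of freedom (51 for the adjusted contrast):

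| Contrast | d = 1.0: estimate/SE | Power | d = 0.62: estimate/SE | Power |
|---|---|---|---|---|
| Averaged group effect | 0.5/0.211 = 2.37 | 64% | 0.309/0.211 = 1.46 | 30% |
| Group-by-time | 1.0/0.344 = 2.90 | 81% | 0.618/0.344 = 1.79 | 42% |
| Baseline-adjusted cued difference | 1.0/0.267 = 3.75 | 96% | 0.618/0.267 = 2.32 | 62% |

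The group coefficient with baseline as reference rejects about 5% of the time whatever d is.

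**Check by simulation.** The mixed model as written, without the covariates, was fitted to 400 simulated trials with a true cued difference of −0.175. Mean estimates were +0.007 (group, baseline reference), −0.080 (averaged group; expected −0.087) and −0.174 (group-by-time). Rejection rates were 3.8%, 27% and 44%. A separate simulation of 20,000 trials at 1.0 SD gave 64.5% for the averaged effect and 80.9% for the change.

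**The case against.** The strongest reply is that the right test is already there. The labelled sentence only introduces the two factors of a repeated-measures design; the next one specifies a model with the group-by-time term, and the tests against 0 cover it. The power section and the daily-life paragraph both state the question as a difference in improvement. An article may leave the deciding coefficient to the full plan.

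Much of this stands. A reader might infer that the plan has no valid test of cueing mode, or that its primary test has only 5% power. The documents do not support that. The interaction is in the model, the averaged group effect is a valid if diluted test under randomization, and no reference level is stated. With cueing as reference, the group coefficient would be the full cued difference (1.0/√(2/27) = 3.67, power 95% at 1.0 SD). The 5% figure needs an unstated coding and an analyst who ignores the interaction.

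A reader might also infer that the 82% is wrong. That does not follow either: the interaction described in section 3.5.1 suggests that task, not baseline versus cueing, is its within-subject factor, so the dilution above need not apply there. What follows is that its power figures do not describe the contrast that section 3.5.2 needs.

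The reply does not remove the label. Both sections call the between-subject effect the cueing comparison, and neither designates or powers the difference in change. That is a statement to correct, not a detail left out.

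**Conclusion.** The point holds in this limited form: the plan contains a suitable contrast but attaches the arm-comparison label to another effect, leaves the deciding coefficient open, and gives power for neither the group-by-time term nor a baseline-adjusted difference.

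At ρ = 0.2 and 27 per arm, relying on the averaged group effect instead of group-by-time costs about 17 points of power at 1.0 SD (81 − 64) and 12 at 0.62 SD (42 − 30). Against the baseline-adjusted contrast the loss is 32 points at both (96 − 64; 62 − 30). The effect sizes are assumptions, so the levels are illustrative; at ρ = 0.2 the ordering is the same at both. The algebra depends only on baseline preceding the cueing set-up, which the protocol states. It is worth correcting because the remedy is cheap and the model form is reused for the secondary and daily-life outcomes.

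**What to change.** In section 3.5.2, state that the effect of cueing mode is tested by one named contrast: the arm difference in the cued condition adjusted for the uncued baseline, by ANCOVA or by the mixed model with a common baseline mean across arms. At minimum, name the group-by-time coefficient. State that the group main effect is not interpreted as a cueing effect. Apply the rule to both primary outcomes and to the secondary and daily-life models.

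Keep the baseline-versus-cueing changes, which the objectives call for, as separate within-arm descriptions that do not decide between arms. The Discussion's criterion, a change seen with personalized but not with fixed cueing, should be aligned with this.

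In section 3.5.1, restate the power for the chosen contrast, with its assumed means.

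Cost: rewording and one new power calculation; no data or procedures change. The restated power may differ from 82%, and the group main effect can no longer be reported as a cueing result. Settling for group-by-time alone would give up power against the adjusted contrast at the plan's correlation (81% versus 96% at 1.0 SD).

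### The planned mixed model compares change scores between arms; constraining the baseline means to be equal would give a more precise treatment contrast at almost no cost

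*Protocol article*

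**What the plan says.** The laboratory model in section 3.5.2 (Statistical analysis) is specified in full. The dependent variable is HbO2 for each person at each of two assessments, uncued and cued. The fixed effects are listed as "i) indicator variable for group assignment (personalized or fixed cueing), (ii) indicators for time points (baseline, cueing), and (iii) group by assessment interaction terms". On covariates it says: "Randomization stratification variables, Hoehn and Yahr, FOG and cognitive status, will be entered into the model as covariates". On the covariance it says: "A random subject intercept will account for correlation between the two repeated measurements within each subject". The uncued value is thus an outcome with its own mean in each arm, not a covariate. Models of the same kind are planned for the laboratory gait and turning outcomes (secondary) and for the home data (exploratory).

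Section 3.5.1 (Power analysis) states one intra-subject correlation: "assuming between-subject variance of 0.08, modest intra-subject correlation of 0.2, and level of significance at 0.05". It belongs to a repeated-measures ANOVA whose interaction is the "differential impact of dual-task versus single-task walking between the personalized- and fixed-cueing groups". The analysed sample is given as "We conservatively assume 54 subjects, 27 for each group (personalized and fixed training), will be included in this analysis". The home comparison is sized differently, for "group differences of at least 0.50 SD for measures of walking and turning in daily life with ANCOVA models", with a covariate R2 of 20%.

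Section 3.1 (Study design and setting) places the uncued assessment at Visit 1 before the unblinded staff explain and configure the assigned mode. The assessor is blinded.

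**The concern.** With two time points, a free group effect at baseline and a random intercept, the group-by-time coefficient is a comparison of change scores. A change score gives the baseline value a weight of 1. The efficient weight is the regression slope, which equals rho when the two variances are equal. The lower the correlation, the more noise the full subtraction adds; below rho 0.5 the change score is less precise than the cued value alone. Covariates that are constant within a person and entered as main effects cancel out of the within-person difference, so they do not sharpen this contrast.

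Precision in the comparison between arms is at stake. The trial expects 54 analysable participants, and its effect sizes are meant to size a later trial. There is also a mismatch: the home comparison is sized by one method and analysed by another.

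**Working it through.** **Inputs.** 27 per arm, alpha 0.05 and the model terms come from the article. Rho between uncued and cued values is not given, so a range is used. Effects are in SD units because the article does not give the HbO2 means. Equal variance at the two assessments and two-sided tests are assumed.

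**The plan's own power figures.** The laboratory figures (82% and 94%) cannot be reproduced without the HbO2 means. The home figure (81.2% with 36 patients) is not reproduced either. With 0.50 SD, R2 0.20 and two-sided alpha 0.02, the non-central t calculation with N - 3 degrees of freedom gives 23.7%; a 1.0 SD difference gives 81.3%. That is a separate matter, and nothing below relies on the 81.2%.

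**Step 1: what the model estimates.** For complete pairs, group-by-time = (mean cued - mean uncued in one arm) - (the same in the other). In 20 simulated complete data sets (27 per arm, rho 0.2, two person-level covariates) the REML coefficient matched the difference in mean change to within 2e-15, and the covariates did not alter it.

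**Step 2: variance per arm, in units of sigma²/n.**
- Change score: 2(1 - rho)
- Cued value only: 1
- ANCOVA or constrained baseline: 1 - rho²
- Ratio of change score to ANCOVA: 2(1 - rho)/[(1 - rho)(1 + rho)] = 2/(1 + rho)

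| rho | Change score | Cued only | ANCOVA / constrained | Ratio |
|---|---|---|---|---|
| 0.2 | 1.60 | 1.00 | 0.96 | 1.67 |
| 0.5 | 1.00 | 1.00 | 0.75 | 1.33 |
| 0.8 | 0.40 | 1.00 | 0.36 | 1.11 |

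At rho 0.2, 20,000 simulated trials gave variances of 0.119, 0.074 and 0.073, a change-to-ANCOVA ratio of 1.65 against 1.67 in theory.

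**Step 3: detectable difference, 27 per arm, 80% power.** SE = sqrt(2 × factor/27).
- rho 0.2: SE is sqrt(2 × 1.60/27) = 0.344 for the change score and sqrt(2 × 0.96/27) = 0.267 for ANCOVA. The detectable differences are 0.98 and 0.76 SD, about 2.86 SEs in each case.
- rho 0.5: multiplying by sqrt(1.00/1.60) and sqrt(0.75/0.96) gives 0.78 and 0.67 SD.
- rho 0.8: multiplying by sqrt(0.40/1.60) and sqrt(0.36/0.96) gives 0.49 and 0.47 SD.

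At rho 0.2, a true difference of 0.76 SD has 58% power as planned and 80% with ANCOVA.

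**Step 4: home sizing against home analysis.** ANCOVA with R2 0.20 implies a factor of 0.80. If the 20% came from the week 1 value, rho = sqrt(0.20) = 0.447 and the planned contrast has factor 2(1 - 0.447) = 1.11, which is 1.38 times 0.80. If it came from time-constant covariates, it would not reduce the variance of the group-by-time contrast. In neither case does the planned model deliver the assumed gain.

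**The case against.** The planned contrast is unbiased and its test is valid. The article calls the trial a pilot that is not meant to be highly powered, and the home analysis is exploratory. All of this stands: the point concerns efficiency and does not show an error in inference.

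A reader might infer stronger claims, which the article does not support:

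- **That 0.2 is the plan's correlation for this contrast.** It belongs to a power model comparing single with dual task. The uncued and cued runs take place within one visit and may correlate more closely; at 0.8 the gain is small. No correlation is given for gait or turning.
- **That the loss can be put in HbO2 units.** The means are not given, and the variance of 0.08 can be read as the total variance or as the between-subject component. With rho 0.2 the second reading makes the total 0.08/0.2 = 0.40.
- **That the covariate adjustment is useless.** It does not sharpen the group-by-time contrast with complete pairs. The plan also compares arms between subjects, where it can matter, and with incomplete pairs the identity is only approximate. In the home model, activity level may vary from week to week and so alter the contrast.
- **That the home R2 refers to week 1.** The article does not name the covariate.

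There is also a fair objection to plain ANCOVA as the remedy. Sections 2 (Objectives), 3.5.2 and 4 (Discussion) call for changes from baseline within each arm, which ANCOVA's treatment contrast does not supply. The constrained model does.

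**Conclusion.** The point holds as an avoidable loss of precision. The direction is certain in large samples for any rho below 1, since 2/(1 + rho) then exceeds 1. The size is not known from the article: a variance ratio of 1.67, 1.33 or 1.11 at rho 0.2, 0.5 or 0.8. The result assumes complete pairs and equal variances at the two assessments.

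Equal baseline means are well founded in the laboratory, because participants are randomised and the uncued assessment precedes explanation and set-up of the assigned mode. At home the assumption is weaker, because week 1 follows brief use of the assigned cueing at Visit 1. The disagreement between the home sizing method and the home analysis method stands whatever the source of the 20%.

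**What to change.** **Laboratory primary and secondary outcomes.** Keep the mixed model with both values as outcomes, but constrain the arms to a common baseline mean: retain time and group-by-time and drop the group main effect at baseline. This preserves the planned within-arm estimates of uncued against cued. ANCOVA of the cued value on the uncued value is an equivalent alternative for the between-arm contrast only. Keep the Hoehn and Yahr, FOG and cognitive-status covariates. Once the baseline is constrained, the estimate depends on the assumed covariance, so an unstructured covariance for the two measurements would avoid relying on equal variances.

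**Power statement.** Restate power for this contrast with an explicit correlation between uncued and cued values, or a range.

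**Exploratory home outcomes.** Make sizing and analysis agree, for example week 2 adjusted for week 1. Name the covariate that supplies the R2, and state the assumption that the Visit 1 cueing does not carry over into week 1.

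**Cost.** A changed model sentence and at most one degree of freedom. No visit, measurement or participant burden changes.
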